## Abstract

**Background:**

Society is facing multiple challenges, including lifestyle- and age-related diseases of major public health relevance, and this is of particular importance when the general population, as well as the workforce, is getting older. In addition, we are facing global climate change due to extensive emissions of greenhouse gases and negative environmental effects. A lifestyle that promotes healthy life choices as well as climate and environmentally friendly decisions is considered a sustainable lifestyle.

**Objective:**

This study aims to evaluate if providing information about a sustainable lifestyle encourages individuals to adopt more nutritious dietary habits and increase physical activity, as compared to receiving information solely centered around health-related recommendations for dietary intake and physical activity by the Nordic Nutrition Recommendations and the World Health Organization. Novel features of this study include the use of the workplace as an arena for health promotion, particularly among office workers—a group known to be often sedentary at work and making up 60% of all employees in Sweden.

**Methods:**

The Sustainable Office Intervention (SOFIA) study is a 2-arm, participant-blinded, cluster randomized controlled trial that includes a multilevel sustainable lifestyle arm (intervention arm, n=19) and a healthy lifestyle arm (control arm, n=14). The eligibility criteria were being aged 18-65 years and doing office work ≥20 hours per week. Both intervention arms are embedded in the theoretically based behavioral change wheel method. The intervention study runs for approximately 8 weeks and contains 6 workshops. The study focuses on individual behavior change as well as environmental and policy features at an organizational level to facilitate or hinder a sustainable lifestyle at work. Through implementing a citizen science methodology within the trial, the participants (citizen scientists) collect data using the Stanford Our Voice Discovery Tool app and are involved in analyzing the data, formulating a list of potential actions to bring about feasible changes in the workplace.

**Results:**

Participant recruitment and data collection began in August 2022. As of June 2024, a total of 37 participants have been recruited. The results of the pilot phase are expected to be published in 2024 or 2025.

**Conclusions:**

Given the ongoing climate change, negative environmental effects, and the global epidemic of metabolic diseases, a sustainable lifestyle among office workers holds important potential to help in counteracting this trend. Thus, there is an urgent unmet need to test the impact of a sustainable lifestyle on food intake, physical activity, and environmental and climate impacts in a worksite-based randomized controlled trial. This study protocol responds to a societal need by addressing multilevel aspects, including individual behavior changes as well as environmental and organizational changes of importance for the successful implementation of sustainable lifestyle habits in an office setting.

**International Registered Report Identifier (IRRID):**

DERR1-10.2196/57777

## Introduction

### Background

Nations around the world, including Sweden, are facing multiple challenges driven by lifestyle- and age-related diseases of major public health relevance, such as diabetes type 2, cardiovascular disease, and cancer [1,2]. It is estimated that physical inactivity in the European population costs each country between €1 and €2 billion (US $1.09 and US $2.18 billion) in health care spending [3]. Moreover, improved adherence to healthy dietary patterns by 20% in the American population has the potential to save more than US $20 billion in costs associated with noncommunicable diseases (NCDs) [4]. This is of particular importance when the general population, including the global workforce, is getting older. Moreover, we are facing global climate change due to extensive emissions of greenhouse gases and substantial negative environmental effects [5]. A lifestyle that promotes both healthy life choices, as well as climate- and environmental-friendly behaviors, is considered a sustainable lifestyle [6,7]. It is important that individuals believe that they can take responsibility for their own lifestyle, but it is also essential that a sustainable lifestyle be encouraged and facilitated at work and through society at large.

Although many Swedish workplaces offer their employees tax-deductible preventive health care services (wellness allowance), such incentives have been used mostly to promote exercise outside of the workplace and have been used predominantly by employees who are already physically active [8,9]. In order to achieve a paradigm shift in the way we think about lifestyle factors and health in relation to work, a sustainable lifestyle in areas such as physical activity and healthful food access needs to be considered when new offices are built and designed in order to encourage and facilitate an active and healthy lifestyle during working hours. Such changes need to be feasible, user-friendly, and attractive, but at the same time, avoid creating undue pressure or feelings of guilt among employees [10,11]. A previous study by our team with 5364 well-educated adults aged 18-45 years showed that participants consumed, on average, 1 meal with meat per day for lunch or dinner, and the carbon footprint from their food consumption was, on average, 4.7 kg greenhouse gas emissions per person per day (CO_2_ equivalents [CO_2_e]), which corresponds to 1.7 tons of greenhouse gas emissions per person per year [12]. As different food sources generate different amounts of carbon emissions, with plant foods generally having lower emissions than animal products [13], there would be substantial climate benefits if more people reduced their intake of beef and increased their intake of plant-based foods. Moreover, epidemiological studies have consistently found that high consumption of plant-based foods, such as fruits, vegetables, legumes, and whole-grain products, reduces the incidence of NCDs, such as obesity, diabetes type 2, cardiovascular diseases, and certain types of cancer [14-16]. Health-enhancing behaviors such as regular physical activity are also linked to reduced risk of NCDs [17]. One form of physical activity is active commuting, such as walking or biking to work, which also has positive climate and environmental dimensions as it does not contribute to greenhouse gas emissions, traffic congestion, air pollution, or noise [18,19]. The above types of behavior changes would result in more nutritious and climate-friendly food habits and increased physical activity, which would impact public health substantially.

### Current Guidelines

To promote good health and prevent major NCDs in the population, the Nordic countries have common dietary recommendations, the Nordic Nutritional Recommendations (NNR) [20,21], and Sweden has adopted the recommendation about physical activity from the World Health Organization (WHO) [22]. However, such preventive actions have consistently had a poor impact on the public’s lifestyle choices, and few community members are aware of these recommendations. Therefore, new ways of impacting people’s lifestyles are needed. Since 60% of all employees in Sweden work in an office setting [23], we suggest that a shift to healthy plant-based food should be encouraged at workplaces in the form of food served at events, catering, coffee breaks, and lunch, and physical activity should be encouraged by facilitating active commuting, walk-and-talk meetings, and other forms of everyday movement during office hours.

### Objective

The overall aim of the Sustainable Office Intervention (SOFIA) study is to promote and facilitate the adoption of a sustainable lifestyle within an office environment, with the dual goals of enhancing public health and mitigating the adverse effects of climate change and negative environmental impact. Specifically, the research aims to assess the effectiveness of promoting sustainable lifestyle choices in the workplace compared to promoting a conventional healthy lifestyle.

## Methods

### Study Design and Sample Size

The SOFIA study is part of a larger mixed-method effort titled *Concepts for the Sustainable Office of the Future* (SOFCO) [24], which is studying how sustainable lifestyles and health may be supported among office workers in Sweden. Here, we describe the SOFIA substudy, which is a 2-arm, single-blind (participants), cluster randomized controlled trial comparing a sustainable lifestyle intervention arm with a healthy lifestyle control arm (Figure 1). The intervention study, which will occur in office sites in the Mälardalen region, Sweden, runs over 8 weeks, with each intervention consisting of 6 workshops occurring every week for the first 4 weeks and then every second week for the last 4 weeks (Figure 2). The data collection will occur at baseline and after 4 and 8 weeks, with the target number of randomly assigned participants per intervention arm being 47 participants each.

**Figure 1 figure1:**
[figure not shown]
A SPIRIT flow chart of the SOFIA study. Based on power calculations from the study CLEAR 2018 (unpublished data), 94 participants will be recruited, accounting for an assumed dropout rate of 10% to 15% after the baseline assessment. SOFIA: Sustainable Office Intervention; SPIRIT: Standard Protocol Items: Recommendations for Interventional Trials.

**Figure 2 figure2:**
[figure not shown]
Timeline for the SOFIA 8-week intervention study, which includes 6 workshops plus a follow-up meeting occurring 2-3 months after week 8. WS: workshops. SOFIA: Sustainable Office Intervention.

### Study Population

The project is being conducted in collaboration with companies in the office sector in Sweden. Company A owns and develops office buildings, is located in a medium-sized city, and houses approximately 35 office workers. Company B coordinates and develops facility management, is located in a large city, and has approximately 400 office workers. Through advertisement at these offices, we will invite office workers to sign up via a short web-based screening questionnaire to confirm eligibility for the study, the number of hours working in their office per week, the office location, and active commuting and food habits, along with their contact information. The questionnaire takes approximately 2-5 minutes to complete and will be administrated using links and QR codes. Eligible study participants are aged 18-65 years and perform office work ≥20 hours per week. Exclusion criteria comprise not having access to a smartphone compatible with the Discovery Tool (such as iPhone 5 or Android 2, 3, or later versions), being blue-collar workers who perform ≥20 hours per week of strength or physical work rather than office work, having mental disabilities, and not speaking Swedish.

### Procedure

Invitations to prospective participants working at the targeted companies will be sent through email, and upon their confirmation of interest, individuals will be subsequently invited to attend a baseline meeting. The primary objective of this meeting will be to provide individuals with comprehensive details about the study, have interested individuals sign the approved human subjects consent form, administer the baseline questionnaire, conduct anthropometrical assessments, and provide participants with a urinary sample test kit. A web-based questionnaire including questions about demographic factors, work environment, food habits, physical activity, workplace-related factors, as well as opinions and actions related to environmental and climate impact from one’s lifestyle, will be administered at baseline. The baseline questionnaire takes between 20 to 30 minutes to complete and will be delivered to the participants’ work email. A shorter version of the questionnaire, with a focus on food habits and physical activity, will be repeated at 4 and 8 weeks (Figure 2). The questions about food intake, diet-related CO_2_e, and physical activity have been evaluated with regard to validity and reliability [28-31]. Urinary samples will be collected at baseline and 8 weeks. Thereafter, participants will be cluster-randomized based on their office’s geographic location.

The interventions will start the following week and contain web-based educational sessions (Multimedia Appendix 1) and discussions about how to change behavior on an individual level to achieve a more sustainable and healthier lifestyle. Around 2-3 months after the final workshop, a follow-up meeting (workshop 7) will be held to discuss changes on an organizational level where participants will be encouraged to invite their workplace managers. All workshops will be in person at or near the participant’s workplace. The leaders of each workshop were trained staff from the researcher team at Mälardalen University with a background in nutrition and physiotherapy, and the same staff attended all workshops, except for the first baseline assessment where extra staff will help out with the logistics of data collection.

### A Framework for Behavior Change

The behavioral change wheel [32] serves as a framework for the novel multilevel (personal plus organizational) intervention, which is based on the framework of the COM-B model, including capability (C), opportunity (O), as well as motivation (M), which together have the capacity to support a change in behavior (B). Capability refers to the resources and skills necessary for the individual to adopt a healthy and sustainable lifestyle, for example, knowledge and culinary skills. Opportunity refers to organizational factors, policies, availability, and accessibility of resources supporting a healthy and sustainable lifestyle, for example, areas for physical activity and food options at work. Motivation refers to internal or personal factors that influence decision-making for adopting a healthy and sustainable lifestyle, such as a desire to improve one’s health, contribute to reducing local food waste, reduce one’s global footprint from food and transportation, and increase work productivity.

### Supportive Structures

The research team will facilitate behavior change among participants using the following behavior techniques: goal setting, self-monitoring, social support, framing and reframing, prompts and cues, action planning, information on behaviors and outcomes of behaviors, information about social and environmental consequences, and lastly, review of behavior goals and outcomes (Multimedia Appendix 2) [33]. The 5 web-based educational workshops will be grounded in the principles of the behavioral change techniques framing and reframing, prompts and cues, as well as information regarding social and environmental consequences. These sessions will actively engage participants in discussions and problem-solving, aimed at fostering action planning, and the study personnel will offer constructive feedback on behaviors and outcomes aligned with the individual goals set by the participants (for a description of the intervention functions, see Multimedia Appendix 3 [32,33]).

Participants will complete short, printed questionnaires at workshops 2, 4, and 6 to establish and assess individual dietary goals; monitor behavioral changes; evaluate goal fulfillment, self-efficacy, and outcome expectations; assess social support types and levels; and identify potential barriers and facilitators related to their dietary goals. Throughout the study, participants will complete these questionnaires for the purpose of self-monitoring and reviewing their progress toward achieving their behavioral goals and process evaluation [34]. The questionnaires take between 1 and 3 minutes to complete and will be administrated in paper format at the workshops; the questions are based on the behavior change wheel and social cognitive theory [32,35]. The collected data will be analyzed and summarized using quantitative methods to determine common perceptions of social factors that support behavioral change, identify facilitators, highlight individual experiences, and pinpoint perceived obstacles to implementing behavior changes.

A digital behavioral support package (guidelines, recipes, culinary skills tips, and food choices) will be provided to support adherence to the recommended advice about sustainable and healthy lifestyles, respectively. Recipes will be provided based on guidelines set by the Swedish Food Agency [36] for the control arm, and recipes contributing to a maximum of 0.5-1.5 kg of CO_2_e per portion developed by the Swedish World Wildlife Fund [37] and the Swedish consumer Agency [38] will be provided to the intervention arm. During the workshops, participants will be served lunch in line with the nutritional recommendations of the NNR [20], which is rich in plant-based food such as vegetables, legumes, seafood, and lacto-ovo-vegetarian options.

In addition, the individual-level education, instruction, and motivational factors for behavior change will be put in the context of environmental and organizational prerequisites for behavior change during workshops 1-4. This will be followed up during the fifth workshop in the intervention study when both arms will also be asked to use the research-supported Stanford Healthy Neighborhood Discovery Tool smartphone app (Discovery Tool) [39,40] to document contextual facilitators, barriers, or missing components in their work-related environments with regard to sustainable and healthy lifestyle. Barriers or problems in the workplaces’ physical, social, and organizational environment will be identified and solutions for change will be discussed and implemented during the final workshops for the intervention and control arm, respectively.

### The Intervention Arm: Sustainable Lifestyle

The participants in the sustainable lifestyle arm will be instructed to follow the current dietary and physical activity recommendations of the Food and Agriculture Organization of the United Nations, WHO, and NNR [6,20,22], as well as to adopt proenvironmental behaviors, defined as actions that minimize harm to the environment and combat climate change [41]. They will also be encouraged to increase active transportation to and from work, such as walking or biking [22]; use active transportation (walking) in and around the office; and break up prolonged sitting. The participants will be instructed to consume organically produced food to the highest possible degree and select food items that generate low amounts of greenhouse gas emissions by reducing their intake of red and processed meats.

### The Control Arm: Healthy Lifestyle

The participants in the healthy lifestyle arm will be instructed to follow the dietary recommendations by NNR [20]. In brief, they will be instructed to increase the intake of fruit and vegetable to at least 500 g per day and follow the recommended distribution of energy from macronutrients, that is, energy coming from fat, protein, and carbohydrates, as well as general recommendations about the “plate model,” the combination of food on the plate, to adhere to the recommended intake. Additionally, participants will be instructed to engage in physical activity corresponding to at least 150 to 300 minutes per week of moderate to vigorous intensity, according to the WHO and NNR [20,22]. Moderate-intensity activities include brisk walking, raking the yard, or biking to work, whereas vigorous activities comprise climbing stairs, jogging, or running [22,42].

### Questionnaire Data

We will use self-administrated web-based questionnaires (Multimedia Appendix 4) to assess quantitative data about study participants and lifestyle factors. The questionnaires are implemented in the online system Survey Generator by Alstra, and a unique and personal link to the questionnaire will be sent to each participant by email. The questionnaires are the same for both the intervention and control arm.

Dietary intake will be assessed using the food frequency questionnaire Meal-Q, developed and validated by us [28,29]. Meal-Q covers five domains of food consumption: (1) habitual intake of food items, dishes, and beverages including alcoholic beverages; (2) portion sizes; (3) eating behaviors; (4) meal patterns; and (5) supplements. Photos of (1) rice, potatoes, and pasta; (2) meat, chicken, fish, and vegetarian substitutes; and (3) vegetables are used to estimate portion sizes. For all other food items, a standard portion size will be used. Data from Meal-Q will be converted to a daily intake of approximately 50 nutrients by linkage to the National Food Composition Table [43] to generate the average intake of nutrients per person and day.

Also, life cycle assessment will be used to assess the carbon footprint of food consumption, covering the entire “cradle-to-grave” impact of products, and expressed as kilogram CO_2_e per kilogram of food products (kg CO_2_e/kg) [44]. In brief, we have collected data from life cycle assessment studies aiming at representing the average consumption pattern in Sweden, and each food item in the dietary questionnaire Meal-Q has been assigned a specific CO_2_e value and generates an average daily value of kg CO_2_e per person [45]. The dietary questionnaire also includes questions about the consumption of organic products, both with the type of food groups or products that are consumed as organic versions and the proportion of organic versions within each food group or product.

Physical activity will be assessed using Active-Q, developed and validated by us [30,31]. Active-Q covers five domains of activity: (1) daily occupational activity; (2) transportation to and from daily occupation; (3) leisure-time activity; (4) exercise; and (5) sleep. Participants report the type, duration, and frequency of various activities in each domain. Data from Active-Q are used to calculate the time spent at different activity levels, daily total metabolic equivalent tasks, and energy expenditure [30,46]. Also, Active-Q includes questions about active transportation, such as walking and biking, to and from daily occupations.

### Urinary Pesticide Residuals

To get an objective measure of the consumption of organic food, we will collect urine samples at baseline and at the end of the study to assess the excretion of pesticide residues. Participants will be asked to collect the first urine in the morning (between 6:00 and 8:00 AM) in 50 mL FALCON polypropylene containers and store it cold until the workshop later the same day (between 11.30 AM and 12:30 PM). Thereafter, all samples will be transported on ice to the Swedish Environmental Research Institute, where samples are to be stored at –80 ˚C until further analysis according to gold standard methods. The results will be calculated as μg pesticide/g creatinine to adjust for differences in urinary concentration.

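### Urinary pesticides are expressed only per gram of creatinine, a denominator that the intervention arm's advice to eat less meat can itself lower

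*Protocol article*

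**What the plan says.** The Urinary Pesticide Residuals section gives the purpose of the measure, "To get an objective measure of the consumption of organic food", and the schedule: the study will "collect urine samples at baseline and at the end of the study to assess the excretion of pesticide residues". Each sample is a first-morning urine. The result is to be expressed as μg "pesticide/g creatinine to adjust for differences in urinary concentration". No second scale and no other dilution adjustment is named.

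The dietary advice differs between the arms. The Intervention Arm section says that participants are "instructed to consume organically produced food to the highest possible degree" and are to "select food items that generate low amounts of greenhouse gas emissions by reducing their intake of red and processed meats". The Control Arm section summarises advice based on the Nordic recommendations: "they will be instructed to increase the intake of fruit and vegetable to at least 500 g per day", plus macronutrient distribution and the plate model. It does not mention meat.

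The Primary Objective section lists lower red and processed meat intake among the outcomes. It uses urinary pesticides to validate organic food consumption and, in exploratory terms, to compare the arms after 8 weeks. Principal Findings anticipates a larger fall in pesticide excretion in the intervention arm.

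**The concern.** Dividing by creatinine corrects for dilution, but a between-arm comparison of the ratio is clean only if treatment leaves creatinine alone. Some urinary creatinine derives from creatine and creatinine in meat, and one arm is explicitly asked to eat less of it. The denominator is therefore measured after randomisation and can respond to the intervention. The baseline sample does not remove the problem, because the shift arises after baseline.

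The direction matters. Lower creatinine in the intervention arm pushes its ratio up, against the anticipated result, and more so the better participants follow the meat advice. A real reduction in excretion could be understated or missed.

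**Working it through.** **The plan's own figure.** There is none to reproduce. The article gives no effect size, variance or power for urinary pesticides; its sample size rests on diet-related CO2e.

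**Inputs from the article.** Scale: μg pesticide per g creatinine. Explicit meat reduction: intervention arm only. Target at study end: 40 per arm (Power Calculations and Randomization).

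**Assumed inputs, not in the article.**
- m, share of urinary creatinine that comes from meat: 5% to 20%.
- r, extra reduction in meat intake, intervention versus control: 25% to 75%.

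**Formulas.** The extra fall in creatinine is g = m × r. With pesticide excretion unchanged, the ratio is inflated by 1/(1 − g) − 1. A true 20% fall in excretion appears as a fall of 1 − 0.80/(1 − g).

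| m | r | g | Inflation of ratio | True 20% fall appears as |
|---|---|---|---|---|
| 5% | 25% | 1.25% | 1/0.9875 − 1 = 1.3% | 1 − 0.810 = 19.0% |
| 10% | 50% | 5% | 1/0.95 − 1 = 5.3% | 1 − 0.842 = 15.8% |
| 20% | 50% | 10% | 1/0.90 − 1 = 11.1% | 1 − 0.889 = 11.1% |
| 20% | 75% | 15% | 1/0.85 − 1 = 17.6% | 1 − 0.941 = 5.9% |

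**Effect on power (illustration).** Take 40 per arm, a two-sided 5% test on the log ratio, participants treated as independent, and an assumed log-scale SD of 0.8. The shift seen is δ = ln(true ratio) − ln(1 − g), with standard error 0.8 × √(2/40) = 0.179 and power Φ(|δ|/0.179 − 1.96). For a true 30% fall and g = 10%, |δ| = 0.357 − 0.105 = 0.251 (from unrounded logs), which gives power 0.29.

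| True fall | g = 0 | g = 5% | g = 10% | g = 15% |
|---|---|---|---|---|
| 30% | 0.51 | 0.40 | 0.29 | 0.19 |
| 50% | 0.97 | 0.95 | 0.91 | 0.84 |

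With an assumed SD of 0.6, power for the 30% fall drops from 0.76 (g = 0) to 0.30 (g = 15%). With SD 1.0 it drops from 0.36 to 0.14. A modest true effect is sensitive to the shift; a large one much less so.

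**The case against.** Creatinine correction is a recognised choice and the article gives its reason for it. The strongest objections are these.

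- **The mechanism and its size come from outside the article.** This stands. The documents support saying that creatinine can fall, not that it probably will or by how much.
- **The contrast in meat intake may be small.** Both arms follow the Nordic recommendations, and the control advice is given only in brief. The workshop lunches in Supportive Structures are plant-rich, with no difference between arms stated. The meat instruction covers red and processed meat only, so other meat or fish may replace it. All this could narrow the differential, but it does not remove the explicit difference in instruction.
- **A condensed article may omit a second scale that the full protocol or analysis plan contains.** That is possible, and the absence of a sensitivity analysis is not the complaint. The point is that the one scale the article fixes can depend on treatment.
- **The consequence is limited.** The arm comparison is exploratory and unpowered, and the bias is towards the null, so this mechanism would not create a false benefit. This stands and keeps the point modest.

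Two stronger readings are tempting. A reader might infer that a true 20% fall could vanish entirely. That needs creatinine to fall 20% more in the intervention arm: even at the top assumed meat share of 20%, r = 20%/20% = 100%, whereas participants are asked only to reduce certain meats. A reader might also infer that the organic-food questionnaire would wrongly appear not to be validated. The article does not say that validation rests on the arm difference, and nothing here calculates the agreement between reported organic intake and excretion.

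**Conclusion.** The point holds in a limited form. The only stated scale for urinary pesticides has a denominator that the intervention can lower, and the resulting bias works against the anticipated finding. Under the assumed 1.25% to 15% extra fall in creatinine, the ratio is inflated by 1.3% to 17.6%. In the middle of the assumed ranges (10% share, 50% extra reduction) the inflation is 5.3%. The true size cannot be known from the article. It rests on the link between meat and creatinine, on the assumed ranges, and on a real difference in meat intake between the arms. It affects how an exploratory comparison is read, not the basis on which the trial was sized.

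**What to change.** Keep the creatinine-corrected result and add two analyses:

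1. Compare the baseline-to-week-8 change in urinary creatinine between arms, as an estimate with a confidence interval. At this sample size a non-significant difference would not rule out a shift of a few per cent.
2. Report the between-arm pesticide comparison on the uncorrected first-morning concentration beside the creatinine-corrected one.

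State in advance that, if creatinine differs by arm, a null or reduced creatinine-corrected difference will not be read as absence of an effect on excretion. Do not require agreement across all scales before claiming an effect, since that would give the affected ratio a veto.

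**Cost.** No new assay is needed, because forming the ratio already requires both the pesticide and the creatinine concentration. The downside is that uncorrected concentrations are noisier because of dilution. A spot-sample creatinine difference can also reflect dilution as well as diet. Specific gravity on the frozen aliquots could help separate the two, at no more than 2 × 94 = 188 readings where volume allows. It should remain optional, because it needs an extra measurement and may itself be partly affected by protein intake.
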